### Study parameters

The primary outcome of the study is HRQL as measured with the PAQLQ-S (standardised activities). The Dutch version of the PAQLQ was validated in children ≥ 6 years and has psychometric properties similar to those reported for the original PAQLQ [30]. Also the HRQL of the main caregiver is assessed with the PACQLQ (paediatric asthma caregiver quality of life questionnaire) [31].

Secondary outcomes are asthma control, psychosocial problems and satisfaction with care. Asthma control is measured by questionnaires such as the Asthma Control Questionnaire (ACQ) [32], the Childhood Asthma Control Test (C-ACT) [33] and the Asthma Therapy Assessment Questionnaire (ATAQ) [34]. Psychometric properties of all asthma control instruments were found to be good [32,33,35]. Lung function with reversibility (pre- en post- FVC, pre- and post- FEV1) and Fraction of exhaled NO^1^ (FeNO) will be assessed according international guidelines [36,37]. Psychosocial problems will be measured with the Dutch version of Strengths and Difficulties Questionnaire (SDQ) that shows good psychometric properties [24]. An adapted version of the Patient-Doctor relationship Questionnaire (PDRQ-9) will be used to measure parent’s satisfaction with provided care to their child by a care provider and other patient-doctor relationship aspects [34].

### Data collection

In the recruitment phase, the parents receive a questionnaire on family characteristics (e.g., socio-economic status, family history of respiratory diseases, composition of family, smoking habits), child asthmatic symptoms, medication use, attitude towards asthma [35]. All participants visit the general practices or outpatient clinic four times during a follow-up period of 9 months. The parents as well as the children fill out a questionnaire at the start and end of the study to measure HRQL, asthma control, psychosocial problems and satisfaction with care. During the first visit, lung function will be measured of subjects in the primary care trial. In specialized care, both lung function and fraction exhaled NO will be measured during the first and last visit. Next, the parents fill out monthly calendars on asthma control, symptoms and medication use of their child. Finally, health care providers, parents and children will be inquired about the satisfaction and user friendliness of implementation of the Pelican using structured questionnaires. Since the Pelican study is a complex intervention, data will be collected for process evaluation.

### Data analysis

The primary analysis is an intention-to-treat analysis, however both explanatory and intention-to-treat analyses will be performed. The effect of the Pelican in primary care will be analysed using multi-level analyses techniques. The effect of the Pelican in specialized care will be assessed using multivariate regression models. A correction for baseline value of the outcome of interest (e.g., HRQL, asthma control) will be added to the model.

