## Methods/design

### Study design

This study consists of two RCTs: one in primary care and one in specialized care. Because the study design, sample size calculation and treatment allocation differ between the trials, these aspects are described separately. All other aspects apply to both trials.

170 participants in primary care will be recruited from 16 general practices in the Netherlands. The primary care study is a multicentre parallel group study with a hierarchical or nested design. This means that all participating patients within a general practices will be allocated to the same treatment group (usual care or intervention group). During visits the usual care group receives care of the GP according NHG (Dutch GP Association) guidelines [22]. Besides usual care, the intervention group will receive recommendations based on the Pelican outcome by a practice nurse as well.

The most optimal study design for intervention studies is a multilevel design to avoid contamination between usual care and the intervention, which is applied in the primary care trial. There are, however, not enough outpatient clinics in the Netherlands to be able to use a multilevel design in specialized care. This means that specialized nurses provide care for both patients of the intervention and those of the usual care group. 100 participants in specialized care will be recruited in 5 outpatient clinics in the Netherlands. The usual care group receives care according to NVK (Dutch Association of paediatric) guidelines of paediatric asthma in the Netherlands of a care provider (e.g. paediatrician or nurse) [23]. The intervention group receives an intervention with the Pelican outcome by an asthma nurse complementary to usual care.

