### Randomisation: treatment allocation

Enrolment of participants will be performed by the general practices or outpatient clinics. Participants can be allocated to the usual care or intervention group. In both trials, the minimization technique will be used to allocate participants to treatment. Minimisation is an advanced randomisation technique as described by Pocock [26,27]. The balance between both groups will be kept with consideration of prognostic factors (categorical variables) as described below with a computer program called Minim.

In the primary care trial general practices will be allocated balanced on the following prognostic factors: 1) number of potential participants for study within GP (<18 or ≥18 patients with the diagnosis asthma between 6–11 years old) and 2) usual asthma care (absence of structured asthma care, structured asthma care for adults or structured asthma care for children).

In the specialized care trial the minimisation technique will be used to force treatment allocation of individual participants with consideration of the prognostic factors age (6–8 years old and 9–11 years old) and level of asthma control (ACQ score <1 and ACQ score ≥ 1).

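### Specialised care: allocation is minimised on age group and ACQ level, but the regression names only the baseline outcome as covariate, so the test is mildly conservative

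*Protocol article*

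**What the plan says.** Under Randomisation: treatment allocation, the Protocol article states: "In both trials, the minimization technique will be used to allocate participants to treatment". In specialised care individual children are allocated "with consideration of the prognostic factors age (6–8 years old and 9–11 years old) and level of asthma control", with the ACQ cut at 1. In primary care the practice is the unit of allocation, balanced on its number of potential participants and its type of usual asthma care.

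Under Data analysis, the specialised-care model is given as follows: "The effect of the Pelican in specialized care will be assessed using multivariate regression models". One adjustment is named, for both trials: "A correction for baseline value of the outcome of interest (e.g., HRQL, asthma control) will be added to the model". No minimisation factor is mentioned for either model.

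Under Study parameters, the primary outcome is the PAQLQ-S. Asthma control, measured with the ACQ among others, is secondary.

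**The concern.** Minimisation removes most of the chance imbalance in age group and ACQ level. If these factors predict the outcome, the treatment estimate varies less from trial to trial than it would under simple randomisation. A regression that omits them does not see this. It counts the variance they explain as residual noise and reports a standard error suited to an unbalanced allocation. The interval is then too wide, the test rejects too rarely under the null, and power is lost.

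Baseline PAQLQ-S does not stand in for either factor. It accounts for them only so far as it is correlated with them, and what matters is what they explain beyond it. The trial has little power to spare: it is sized for 80%, and the Discussion expects contamination between arms to shrink the difference.

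**Working it through.** **Inputs from the Protocol article.** Specialised care: 100 children, 15% dropout, α = 0.05 (taken as two-sided), power 0.80, 10% responders under usual care and a 25-point difference, so 10% against 35%.

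**Reproducing the planned size.** With pooled proportion 0.225,

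n per arm = [1.96·√(2·0.225·0.775) + 0.842·√(0.10·0.90 + 0.35·0.65)]² / 0.25² = 42.6, so 43.

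Dividing by 0.85 gives 51 per arm, 102 in total; multiplying by 1.15 gives 50 per arm, 100 in total. The stated 100 is reproduced closely. With 100 × 0.85 = 85 evaluable children (42.5 per arm), power is 79.9%.

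**Closed-form check of the direction.** Let R be the share of the variance left after baseline that the two factors explain, and suppose balance is exact. The omitting model has variance proportional to 1, while the estimate varies in proportion to 1 − R. Then, with Φ the standard normal distribution function:

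- model SE / true SD = 1/√(1 − R)
- type I error = 2·[1 − Φ(1.96/√(1 − R))]
- power, factors omitted = Φ(0.842/√(1 − R))
- power, factors included = Φ(2.802/√(1 − R) − 1.96)

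| R (assumed) | SE ratio | Type I error | Power omitted → included |
|---|---|---|---|
| 2% | 1.010 | 4.8% | 80.2% → 80.8% |
| 5% | 1.026 | 4.4% | 80.6% → 82.0% |
| 10% | 1.054 | 3.9% | 81.3% → 84.0% |
| 20% | 1.118 | 2.8% | 82.7% → 87.9% |

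**Simulation.** 4,000 runs per setting, 85 evaluable children, minimisation on two two-level factors, least squares on a continuous score. The treatment effect was set for about 80% power with baseline adjustment alone. Assumptions not in the article: baseline correlation 0.5, deterministic minimisation, and the values of R. Clinic variance is zero in this table.

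| R (assumed) | SE ratio, factors omitted | Type I error, omitted → included | Power, omitted → included |
|---|---|---|---|
| 2% | 1.02 | 4.3% → 4.4% | 79.3% → 79.9% |
| 5% | 1.04 | 4.0% → 4.5% | 79.8% → 81.2% |
| 10% | 1.05 | 3.8% → 4.9% | 78.8% → 82.1% |
| 20% | 1.11 | 3.0% → 5.1% | 80.7% → 86.7% |

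Monte Carlo error is √(0.05·0.95/4000) ≈ 0.3 points for the type I error and √(0.8·0.2/4000) ≈ 0.6 points for power. At R = 2% the two models barely differ in type I error (4.3% against 4.4%), and the closed form gives 4.8%. Most of that shortfall from 5% is therefore simulation noise. The effect is clear from about 10% upward.

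**Clinic.** With clinic outside the minimisation and omitted from the model, the SE ratio was 0.97 to 1.01 and the type I error 4.7% to 5.6% for intraclass correlations of 0.04 and 0.10. The standard error is not too large. Adding four clinic indicators changed power from about 79.3% to 77.8% at a correlation of 0, from 77.4% to 75.9% at 0.04, and from 79.3% to 80.5% at 0.10.

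**The case against.** The strongest objection is that the article never says baseline is the sole covariate. Its analysis section is short, a multivariate regression leaves room for other terms, and a full plan may list them. This stands as a limit: a reader might infer that the minimisation factors are excluded, and the text does not say so. The point survives because the article does more than stay silent. It sets out the balancing factors in detail, then names an adjustment that leaves them out. Followed as written, the analysis does not match the allocation.

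A second objection is that the harm is small and in the safe direction. This is correct. False positives are not inflated, the balanced factors introduce no bias, and the size depends on an assumed R. When the ACQ itself is the outcome, the baseline correction already covers one of the two factors.

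Third, the hypothesis and sample size concern the proportion of children improving by 0.5 points. For such a binary endpoint in a logistic model, adjustment raises the standard error of the log odds ratio even as power rises. The statement about the standard error is therefore limited to the continuous score.

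Two wider readings are tempting and are not supported:

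- **Clinic.** The article says "100 participants in specialized care will be recruited in 5 outpatient clinics in the Netherlands" and names clinic in neither the minimisation nor the model. A reader might infer that this too makes standard errors too large. It does not, because the mechanism needs a factor that was balanced. The article also leaves open whether minimisation is run within each clinic or across all five. If across, and treating each clinic as 20 children under simple randomisation, the chance of at least one split of 14:6 or worse is 1 − (1 − 0.115)⁵ ≈ 46%. That figure falls away if minimisation is run within clinics; the standard-error argument would then reach clinic as well.
- **Primary care.** A reader might infer that the practice-level factors must be added there too. "The effect of the Pelican in primary care will be analysed using multi-level analyses techniques", and practice is already the cluster. The added terms would take 1 + 2 = 3 of the 16 − 2 = 14 practice-level degrees of freedom, at about 2 points of power if they explain nothing. No benefit was calculated to set against that.

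**Conclusion.** The point holds for the specialised-care trial, for age group and ACQ level, with the PAQLQ-S analysed as a continuous score. With the named covariate alone, the model standard error exceeds the true variability by about 2% to 11%, and the type I error is about 4.3% to 3.0%, for R from 2% to 20%. The power lost is about 1 to 3 points for R of 2-10% and about 6 points at 20%. The direction follows from the design; the size rests on R, for which the article gives no figure, and is negligible at the low end. This is an improvement available at almost no cost. It is not a threat to the trial's validity, and the planned sample size does not change.

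**What to change.** In Data analysis, state that the specialised-care regression includes age and baseline ACQ alongside the baseline value of the outcome. Where the ACQ is itself the outcome, only age is new. Fix this before outcome data are seen.

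No extra children or measurements are needed: both variables must be known at allocation, and asthma control is measured at the start of the study. The model loses two degrees of freedom, from 85 − 3 = 82 to 80, which is trivial.

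Optional, and not part of the point upheld: say whether minimisation is run within or across clinics and how clinic enters the analysis, and decide whether the practice-level factors are worth their degrees of freedom in primary care.

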### Process evaluation and cost-effectiveness analysis

The implementation of the Pelican in health care is a complex intervention [38]. A detailed process evaluation is crucial to evaluate what the active ingredients are and how they are exerting their effect. Potential barriers and facilitators of implementation are screened in every phase of the study, starting at the completion of the Pelican instrument by the child at home, the use of the Pelican instrument during the medical visit by the health care professional and finally the influence on asthma specific HRQL [39].

A cost-effectiveness analysis (CEA) from a societal perspective will be performed and reported according to national and international guidelines [40,41]. The costs included will be program costs, direct medical costs and indirect costs measured in their natural units and transformed to costs using real prices and standard reimbursement of expense tariffs. An effect is defined as a relevant change in HRQL (i.e., ΔPAQLQ ≥0.5 point) in the denominator and the total of all relevant costs in the nominator.

### Ethics

Ethical approval is obtained from the Medical Ethics Committee of the Arnhem-Nijmegen region in the Netherlands. The study protocol is extensively studied by: The Dutch Asthma Foundation, NutsOhra and Radboud University Nijmegen Medical Centre (RUNMC). This trial is registered by clinicaltrial.gov (NCT01109745).

## Discussion

Patient centred care, especially in chronic diseases, has a growing need to implement information on health related quality of life (HRQL) next to clinical and physiological measures. Although several quality of life instruments for paediatric asthma patients already exist, the Pelican instrument distinguishes itself because of its applicability in regular medical care. In this article, we presented the methodological design of the Pelican study. Our primary research question is whether the use of the Pelican will improve the asthma-related quality of life in children with asthma from 6–11 years old. The secondary research questions are whether the use of the Pelican intervention will improve asthma control, satisfaction with care and HRQL of the parent. Furthermore, it will be evaluated whether the Pelican is able to detect and reduce psychosocial problems. The study consists of two RCTs with a follow-up of nine months performed in primary and specialized care. Although the study design, sample size and treatment allocation of participants differ between both trials, the research questions and data collection will be identical. The trial in primary care will be a multilevel design, while participants within outpatient clinics of specialized care will be randomly allocated to the usual care and intervention group.

The Pelican study has a couple of strong characteristics. In this study, we choose to add another HRQL instrument to the data collection besides the Pelican instrument as an independent HRQL measurement to answer our primary research question. Another strong characteristic of this study is that the intervention will be investigated in both principal health care settings for childhood asthma, doing justice to the differences that exist in organisation and patient characteristic between primary and specialized care. For example, paediatric asthma patients in primary care show lower disease severity compared to patients in specialized care [7]. This could imply different levels in room for improvement in HRQL and thus could lead to different effect results. Performing two trials which are methodologically optimised to the health care setting leads to better validity and reliable results of treatment effect and cost effectiveness analyses. Furthermore, a detailed process evaluation will be done to map barriers and facilitators of the treatment.

However, some drawbacks must be mentioned. It is impossible to perform a double-blind RCT because patients will be aware of the treatment group allocation. In addition, being a subject in an intervention study will cause the Hawthorne effect, easily leading to a favourable response [42-44]. A specific limitation of the primary care trial is the frequency of medical visits. To keep up scientific comparability between the two trials and actively work on a treatment plan with the patient, the frequency of four medical visits during a period of nine months was set. This frequency of medical visits is usual in specialized care but doubled the frequency of visits in primary care compared to the recommendations in national guidelines. Usual care in the primary care study is, therefore, best described as ‘enhanced usual care’ [45]. Increasing contact time between child and care provider may give more favourable results. This effect is expected to be equal in both study arms in the primary care trial. Ideally, a usual care group without any protocol enhancements would have been added to the RCTs. Furthermore, we choose to let the Pelican intervention be performed by a practice nurse. Nurses play an increasing important role in health care for chronic patients, such as diabetes and COPD patients. Involvement of paediatric nurses is already part of usual care in most paediatric outpatient clinics while paediatric asthma management in primary care is usually provided by family physicians without involvement of nurses. A recent study of Kuethe et al. (2011) suggested that the level of asthma control in children managed by an asthma nurse is not inferior to traditional management by primary or specialized care physicians [46]. Our choice of practice nurse involvement was made with the eye on expected future changes in paediatric asthma care in family practices.

A limitation in the specialized care trial is the risk on contamination bias. The specialized nurses in outpatient clinics provide care for patients of the intervention and usual care group. Although nurses were instructed not to use intervention techniques in the usual care group, contamination bias is unavoidable. The trained nurse in outpatient clinics might unintentionally apply training aspects (such as shared decision-making) during treatment of patients in the usual care group and may potentially minimize the difference in outcomes between the two treatment groups.

In conclusion, the aim of this study is to assess the effectiveness of the Pelican in primary and specialized care through a self-management treatment with the aim of improving asthma-related quality of life in children with asthma from 6–11 years old. If the Pelican proves to be effective and efficient, implementation of this instrument in usual care for paediatric asthma will be recommended. Although the implementation of the Pelican intervention will be evaluated in two almost equal RCTs, it was necessary to adjust the design of both trials to fit the concerning settings. Although, different study design characteristics lead to less comparability between the two trials, the unique feature of this project is that we do not need to extrapolate study outcomes to another care settings based on numerous assumptions, as the intervention is evaluated simultaneously in both major care settings.

## Abbreviations

ACQ: Asthma control questionnaire; ATAQ: Asthma therapy assessment questionnaire; ACT: Asthma control test; C-ACT: Childhood asthma control test; FeNO: Fraction exhaled nitric oxide; FEV1: Forced expiratory volume in one second; FVC: Forced vital capacity; GP: Family physician/practice; HRQL: Health related quality of life; PACQLQ: Paediatric asthma caregiver quality of life questionnaire; PAQLQ: Paediatric asthma quality of life questionnaire; Pelican: Paediatric electronic quality of life instrument for childhood asthma instrument in the Netherlands; PDRQ-9: Patient doctor relationship questionnaire; SDQ: Strengths and difficulties questionnaire; UMC: University medical centre.
